### Data Analyses

Every participant received a pseudonym so that data from the different sources (interviews, questionnaires, physiological data from the E4, EMAs from the smartphone) can be grouped. Raw data analyses and analyses of data on an individual level are being conducted by the Fraunhofer IGD, an institution that is independent of UMR, ensuring data privacy. The UMR will receive the preprocessed, averaged data for further evaluation processes.

The experimental setup consisted of a local server that, via a locally installed network, only ensured the station’s data flow by transmitting data from smartphones and the wristbands. Local access to the server was limited by password-protected log-in. Data were also stored in pseudonymized form, so that no clear names could be found in the files. Data were automatically forwarded from the smartphone once a day to a server within the UMR via Wi-Fi connection. There, the collected information initially remained locally on the hard drive. At regular intervals, a Fraunhofer Institute employee brought along an encrypted data storage device on which he or she created a local backup copy on and transferred it to a computer within the Fraunhofer Institute. This prevented unauthorized access by unauthorized people.

The participants were informed in advance about the guarantee of data security, including the scope of the data collected and the duration of data storage, in their written consent form. These aspects were explained to an ethics committee and confirmed by a positive ethics vote.

The raw data were collected with the Empatica E4 device and stored in CSV files. Each parameter was sampled at the maximum available rate provided by the Empatica E4 firmware. The parameters included interbeat intervals (IBI) sampled at 1/64 second, blood volume pressure sampled at 64 Hz, EDA sampled at 4 Hz, temperature sampled at 4 Hz, and acceleration sampled at 32 Hz.

All parameters were stored with a Unix time stamp to allow the proper selection of intervals.

The EDA data were decoupled using the NeuroKit2 Python library so that the tonic component (skin conductance level) and the phasic component (skin conductance response) could be extracted.

Since the Empatica E4 wristband saved IBI only when the signal quality is sufficient, IBI data can include missing values. The IBI data were used to determine the HRV and HR by applying the following equation:

The acceleration data were fused to a 3D vector by applying the following equation:

All algorithms for data extraction were written in Python using Jupyter Notebooks and the *Pandas*, *Numpy*, *SciPy*, *Matplotlib*, and *NeuroKit2* libraries.

For stress detection analysis, all stress events marked with a button press will be identified, and windows surrounding this event will be extracted and averaged, leading to one value per stress event per participant. Analogously, the windows surrounding a scan of the NFC tag “relaxation” and the baseline windows will be extracted and averaged as well. Descriptive and inferential statistical analyses will be applied using IBM SPSS Statistics 30. Weighted ANOVAs for correlated samples will be computed to compare the stressful events and the baseline for each physiological parameter.

To examine the predictability of experiencing stress, the subjective ratings given in the EMA will be used as ground truth. Surrounding the EMA, data windows will be extracted from the data for each physiological parameter. A linear regression will be computed with the subjective stress level (EMA) as the dependent variable and entering the means of the physiological variables (HR, HRV, tonic EDA, phasic EDA, temperature, and acceleration) as independent variables. Artificial intelligence approaches will be used to analyze the data where appropriate.

With the data for daily occupancy of patients and the total number of nurses on the same day, we will be able to calculate the relationships of these 2 variables with stress. The minimum occupation level according to the recommendation from the German Society for Palliative Medicine (*Deutsche Gesellschaft für Palliativmedizin*) on staffing in palliative wards [30] of 1.4 nurses per patient will be used as a cutoff to create two subgroups of “well-staffed” and “under-staffed.”

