#### Body-Worn Equipment

The results of measured electrodermal activity (EDA), HR, and skin temperature should provide information about an SNS reaction to stress [14]. All these parameters are recordable with the Empatica E4 (Empatica Inc) research wristband. Thus, to measure the physiological stress reaction, we used the commercially available Empatica E4 wristband [27]. The E4 wristband possesses a photoplethysmography sensor and 2 electrodes to measure the galvanic skin response at the wrist. It was used to measure pulse, HRV, EDA, and body temperature (surface). The automatic data preprocessing was bypassed, since this would require sending the sensitive data to an alien server. To circumvent these international servers for reasons of data protection, the code of the E4 had been altered, allowing the extraction of raw data. Raw data were then sent to the smartphone, which is also part of the study’s setup, and stored on the phone’s memory until transferred to a local server. The E4 had no display and thus provided no feedback to the participants that could interfere with or distort the measurement. LEDs provided the necessary feedback on the functionality of the wristband, and additional feedback on functionality (and connectivity) was given in the corresponding smartphone app.

In addition to the LED, allowing event marking (ie, a real-time annotation) via tapping the button deposits a record in the session file. The record included the time of the button press (expressed as a Unix time stamp in UTC), which was synchronized with the initial time of the corresponding session. Feedback on the button press was given both visually (illuminating the LED) and audibly (beeping). The button press was used for 2 purposes: (1) logging an event of subjectively perceived stress (a single button press) and (2) logging the event of disinfecting one’s hands (as this can alter the EDA; 2 consecutive button presses).

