### Sample and Recruitment

The PCU at UMR, with its 14 beds, is the largest PCU in Mecklenburg-Western Pomerania, Germany. It employed 13 full-time nurses and 5 part-time nurses who work in a 3-shift system during the study implementation in 2021. Study participants had to be older than 18 years, their working time had to have a minimum of 20 hours per week, they had to have proficiency in written and spoken German, and they had to be employed at the palliative care unit at the Rostock University Medical Centre (inclusion criteria). Exclusion criteria comprised of nonconsenting capacity and nonfulfilment of all inclusion criteria. For the DiPa study, all 18 nurses working in the UMR PCU, who partly specialize in palliative care, were invited in December 2020 to participate in the study by presenting the procedure and aims of the project in a lecture as well as in a written inquiry. The measurement period for each participant was 6 weeks allowing for a total measurement duration of 3 months.

A power analysis was not conducted as the population was prespecified (N=18), rendering the need for an accruing sample. In the end, 12 nurses agreed to participate, resulting in a participation rate of 67% (12/18).

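### The stress-versus-baseline ANOVA is set up on one value per button press with an undefined weight, so the plan does not secure the nurse as the unit of analysis; on some readings the test is too liberal

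*Protocol article*

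**What the plan says.** Under Data Analyses, the article describes the extraction of button-press stress events: "windows surrounding this event will be extracted and averaged, leading to one value per stress event per participant". The comparison data are treated alike: "Analogously, the windows surrounding a scan of the NFC tag “relaxation” and the baseline windows will be extracted and averaged as well". The test follows: "Weighted ANOVAs for correlated samples will be computed to compare the stressful events and the baseline for each physiological parameter". SPSS 30 is named as the software.

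Three things are not fixed: what a row of the ANOVA is, what the weight is, and whether a nurse effect is included. The only unit named for the stress value is the event.

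Under Body-Worn Equipment, a single press marks stress that the nurse herself perceives, so the number of events per nurse is hers to choose. Under Sample and Recruitment, 12 of 18 nurses took part, and "The measurement period for each participant was 6 weeks allowing for a total measurement duration of 3 months". Many events per nurse, in uneven numbers, are therefore possible.

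**The concern.** All presses by one nurse share her personal reaction, that is, how far her heart rate or skin conductance moves from her own baseline when she feels stressed. Comparing events with baseline as correlated samples removes her general level. It does not remove this shared difference. If presses are counted as separate observations, the error term is the scatter between events, and the test behaves as if there were far more than 12 independent people.

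The article's introduction gives as its primary goal showing that stressors can be identified and stress reactions measured with wearables. This ANOVA is the direct inferential check on whether a reaction appears, and it is repeated for each physiological parameter. A p-value that is too small would support a claim about nurses that 12 nurses may not bear, and the results are meant to feed preventive measures.

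**Working it through.** The article gives no alpha, power or error rate for this test, so there is no stated figure to reproduce. The participation rate checks: 12/18 = 67%.

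**Inputs.** From the article: 12 nurses, one value per press, self-initiated presses. Assumed: two-sided alpha 5%, true mean reaction zero, within-nurse SD of the event-minus-baseline difference 1, between-nurse SD of that difference (τ) 0 to 0.5, mean 10 to 40 presses per nurse, with equal or skewed (negative binomial, shape 1 or 2) counts.

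**Events as rows, equal counts.** The share of variance between nurses is ICC = τ²/(1 + τ²). The true variance of the mean exceeds the assumed one by D = 1 + (n − 1) × ICC, and the rejection rate is about P(|Z| > 1.96/√D).

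| τ | n | ICC | D | 1.96/√D | Rejection |
|---|---|---|---|---|---|
| 0.2 | 10 | 0.04/1.04 = 0.0385 | 1.346 | 1.689 | 9% |
| 0.3 | 20 | 0.09/1.09 = 0.0826 | 2.569 | 1.223 | 22% |
| 0.5 | 40 | 0.25/1.25 = 0.20 | 8.80 | 0.661 | 51% |

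Simulation agrees: 9% to 50% with equal counts. With skewed counts it gives 11% to 61%.

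**Events as rows, unequal counts.** Replace n by Σn²/Σn. Take 240 events split 100, 60, 30, 15, 10, 8, 5, 4, 3, 2, 2, 1. Then Σn² = 14,948 and Σn²/Σn = 62.3. At ICC 0.05, D = 1 + 61.3 × 0.05 = 4.06 and rejection is about 33% (simulated 33.5%). With 20 presses each, D = 1.95 and rejection is about 16% (simulated 15.8%).

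**Is the weighting the cause?** Weights of 1/n per event give every nurse the same total influence. At ICC 0.1 they still give 25.3% (equal counts), 28.4% (moderately unequal, 5 to 40) and 46.6% (the skewed split). Unweighted events give 25.0%, 29.1% and 46.9%. The driver is counting events as independent.

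**Press counts as frequency weights on nurse means.** With 20 presses each, the t statistic is inflated by √(239/11) = 4.66. The effective critical value is 1.97/4.66 = 0.423 on 11 df, and rejection is 68%. This reading fails even when nurses do not differ.

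**Nurse means weighted by press count, 11 df.** About 5% with equal counts and about 6% to 14% with the skewed negative binomial counts. In the fixed splits it is 4.9% to 7.8% when moderately unequal. In the skewed split it is 17.6% to 29.9% at ICC 0.05 to 0.5. There the top two nurses supply 160/240 = 67% of events, and the effective number of nurses is 240²/14,948 = 3.9.

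**Unweighted nurse means, 11 df.** About 4% to 5% throughout.

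**No differences between nurses (τ = 0).** Unweighted events as rows, count-weighted nurse means with 11 df, and unweighted nurse means all stay near 5%.

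**The case against.** The strongest reply is that the text does not make the event the row of the ANOVA. An ANOVA for correlated samples also fits one stress mean and one baseline mean per nurse, and a condensed article may leave rows and weights to an analysis plan that is not shown. Both points stand, and they are why the conclusion is conditional. They do not dispose of it: the article names the event as the unit of the stress value, goes straight from there to the test, and adds a weighting that plain nurse means would not need.

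A reader might infer that the weighting lets frequent pressers dominate and so produces false stress reactions. The article does not support that. The weight is undefined, 1/n weights would do the opposite, and events as rows are too liberal even when all nurses press equally often. Nor is weighting nurse means by count wrong in every case where nurses differ; with near-equal counts it holds its level.

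It can also be said that the primary outcome is feasibility and that the test may only describe marked events on one ward. That lowers the stakes. Still, under that reading the result should not be worded as a reaction of palliative nurses.

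**Conclusion.** The concern holds conditionally. The sentence as published does not secure a valid test, because it goes from one value per press to a weighted comparison without bringing the data back to the 12 nurses.

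- **Presses as rows:** too liberal once nurses differ in reaction, about 9% to 61% at a nominal 5% under the assumed SDs and counts.
- **Press counts as frequency weights on nurse means:** too liberal regardless, 68% in the example with 20 presses each.
- **Nurse means weighted by count, 11 df:** inflated only when counts are clearly unequal, about 6% to 14%, and more under extreme skew.
- **Unweighted nurse means:** sound.

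Press counts and between-nurse variation are assumptions throughout. The percentages show what is possible, not what this study will find, and it cannot be said from the article that its p-values will be wrong.

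**What to change.** State the nurse as the unit. For each parameter, average the stress windows to one value per nurse and the baseline windows to one value per nurse, and run an unweighted paired comparison over 12 nurses with 11 df. Alternatively, fit a mixed model to all events with a random nurse intercept and a random nurse stress effect. Drop any weighting by event count. Dropping the weighting alone, with events kept as rows, would not cure the problem.

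Report events per nurse only in aggregate, for example median and range. Listing each nurse's count or own difference would conflict with the commitment under Ethical Considerations to give the employer group means only.

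The change is to wording; the data and software stay the same, and the article describes these tests as still to be run. The cost is wider intervals and fewer significant parameters. At a true effect of 0.4 SD, between-nurse SD 0.3 and a mean of 20 presses with strongly skewed counts, the nurse-level test has about 73% power, against an apparent 98% with events as rows. The difference is not a real loss, since the 98% belongs to a test that rejects about 32% of the time under the null in the same setting.

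### The stress-versus-baseline ANOVAs do not adjust for movement, although acceleration is recorded, so exertion in nursing work could be reported as a stress reaction

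*Protocol article*

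**What the plan says.** All of the following is in the protocol article, under Data Analyses unless another section is named.

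- **Stress windows.** For each button press, "windows surrounding this event will be extracted and averaged, leading to one value per stress event per participant".
- **Comparators.** In the same way, "the windows surrounding a scan of the NFC tag “relaxation” and the baseline windows will be extracted and averaged as well". How baseline windows are chosen is not stated.
- **Test.** "Weighted ANOVAs for correlated samples will be computed to compare the stressful events and the baseline for each physiological parameter". No covariate is named.
- **Acceleration.** The sampling rates include "temperature sampled at 4 Hz, and acceleration sampled at 32 Hz". The signal is also processed: "The acceleration data were fused to a 3D vector by applying the following equation". Its one explicitly named analytic use is as an independent variable in the linear regression on the momentary stress rating, where it is listed among the physiological variables.
- **Interpretation.** Body-Worn Equipment treats skin conductance, heart rate and skin temperature as informative about a sympathetic reaction to stress.

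**The concern.** The comparison is meant to show that the wearable picks up stress. That inference needs stress and baseline windows to be alike in other influences on the signals, or the difference to be removed in the analysis. Movement is the obvious such influence, and the article itself gives grounds to expect it to matter:

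- Physiological Stress Model explains that muscles need oxygen and that heart rate and breathing rise to supply it. It also ties energy provision to body temperature and sweating. Exertion would plausibly act on the same signals.
- Burden in Palliative Caregiving names the moving of patients among activities felt as heavy burdens, so perceived stress and exertion plausibly coincide.
- One comparator is a relaxation tag, which suggests a quieter state.
- Body-Worn Equipment has nurses log hand disinfection because it can change skin conductance. The authors thus recognise that a non-stress influence needs handling, but the article states no such safeguard for movement.

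If the windows differ in activity, a significant result would not by itself show that stress reactions were measured.

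**Working it through.** **The plan's own figures.** The article states no effect size, alpha, SD or power for this comparison, and Sample and Recruitment says that no power analysis was done. There is no planned figure to reproduce. The participation rate nearby is correct: 12/18 = 66.7%, stated as 67%.

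**Set-up of the illustration.** Only the 12 nurses come from the article; everything else is an assumption.

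- 12 nurses, 10 stress and 10 baseline windows each, and no true stress effect.
- d = difference in mean acceleration between stress and baseline windows, in within-nurse SDs.
- R² = share of the within-nurse variance of the parameter that is due to movement.
- Model: parameter = nurse effect + √R² × acceleration + √(1 − R²) × noise.
- Unadjusted test: paired test on nurse means (a two-condition repeated-measures ANOVA), two-sided 0.05.
- Adjusted test: the same after removing acceleration with the pooled slope estimated within nurse and condition.
- 3,000 runs per setting.

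**Expected spurious difference.** This is d × √R². For d = 0.5 and R² = 0.25 it is 0.5 × 0.5 = 0.25 SD (simulated 0.253). The standard error of the mean difference is √(2/(12 × 10)) = 0.129 SD, so the shift is 0.25/0.129 = 1.94 standard errors. Over all settings with d > 0, the simulated bias runs from 0.08 SD (d = 0.25, R² = 0.10) to 0.71 SD (d = 1, R² = 0.50).

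**False-positive rates.**

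| d | Unadjusted, R² = 0.10 | Unadjusted, R² = 0.25 | Unadjusted, R² = 0.50 | Adjusted, range over R² |
|---|---|---|---|---|
| 0 | 5.0% | 4.6% | 4.9% | 4.6–4.9% |
| 0.25 | 8.1% | 13.9% | 25.2% | 4.4–4.8% |
| 0.5 | 19.9% | 43.2% | 69.7% | 4.8–6.4% |
| 1.0 | 60.6% | 93.4% | 100% | 7.4–7.9% |

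After adjustment the mean bias is about zero in every setting. The rate rises to nearly 8% at d = 1 because this simple adjusted test ignores the uncertainty of the estimated slope; a model that estimates slope and condition together takes it into account. With d = 0 there is no inflation to correct, and adjustment does no harm.

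**The case against.** **Acceleration may itself be tested.** The article counts it among the physiological variables, so the ANOVAs may include one with acceleration as the outcome. This stands, and it means that the plan cannot be said to disregard acceleration. Such a test would reveal a movement difference; it would not remove that difference from heart rate, HRV, skin conductance or temperature.

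**Physical load is partly of interest.** Apparatus, Overview aims to describe the working day in terms of both physical and psychological stress. This stands too, and is a reason to report both analyses. The unadjusted ANOVA alone cannot separate the two.

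**The comparison is not the only support.** Potential Outcomes and Impact makes feasibility of generating data the primary outcome and correlations secondary, and the regression on momentary ratings does contain acceleration. This limits the weight of the point. However, the Introduction describes the primary goal as including the feasibility of measuring stress reactions with wearables, and this contrast bears on that.

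**A full analysis plan may add the adjustment.** It may. But the article already names the test and its contrast, and brings in acceleration as a predictor only in the regression that follows.

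**Signal filtering.** The wristband "saved IBI only when the signal quality is sufficient". That rule covers interbeat intervals only. It does not remove a genuine rise in heart rate from exertion, and it does not protect skin conductance or temperature.

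Two stronger readings are tempting and are not supported. A reader might infer that heart rate and HRV in active windows come only from quiet seconds; the article does not name movement as the cause of missing intervals. A reader might also infer that the weighting lets a few nurses who press often dominate; the article gives neither the weights nor any press counts.

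**Conclusion.** The concern holds as a problem of possible confounding. As written, the ANOVAs compare each parameter between stress and baseline without adjustment for movement, and a movement difference between the windows would be carried into the result.

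Its size cannot be determined from the article. It depends on the movement difference, which is unknown because baseline windows are not defined, and on how strongly each parameter follows movement. Under the assumptions above, the false-positive rate ranges from the nominal 5% to 100%. The figures also assume equal numbers of windows per nurse and no variation between nurses in the condition effect.

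A reader might infer that any significant difference will be movement rather than stress. The article does not support that: if stress and baseline windows are equally active, there is no inflation. The change is worth making before the results are interpreted, but it concerns a supporting analysis and does not touch the feasibility of collecting the data.

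**What to change.** 1. Report mean acceleration for stress, relaxation and baseline windows.
2. Analyse the window-level values of each parameter in a linear mixed model with condition as fixed effect, window acceleration as covariate and a random intercept for nurse. Add a random condition slope only if 12 nurses allow it to be estimated. Alternatively, draw baseline windows of similar acceleration from the same shift.
3. Report the planned unadjusted ANOVA alongside. Interpret a difference as a stress reaction beyond movement only where the adjusted analysis supports it.

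**Cost.** Analysis code only: the acceleration signal is already stored with time stamps, and no new data are needed. The downside is that stress effects that act through movement will be estimated smaller in the adjusted model, which is a further reason to show both results.

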In the same line, introducing repeated prompts during the workday (the EMAs)—together with the aforementioned use of technology—can act as a further stressor. While this method enabled us to capture real-time self-reports of perceived stress and contextual factors, it may have inadvertently increased participants’ cognitive load or interfered with task performance, thus acting as an additional stressor. This reactivity to the assessment process itself could potentially amplify or confound the stress responses we aimed to measure.

Nonetheless, EMA offers critical advantages that justify its use. Unlike retrospective questionnaires, EMA minimizes recall bias and allows for the assessment of stress as it unfolds in the natural work environment, providing high ecological validity. This approach also enabled us to capture dynamic fluctuations in stress levels across the workday and to relate them temporally to physiological stress markers. Importantly, the combination of EMA and physiological measures enhances our ability to understand the complex interplay between subjective experience and somatic stress responses.

Still, the potential reactive burden introduced by the method should be treated as a confounding variable. To mitigate its potential confounding effect, the EMA protocol was designed to be minimally intrusive. The number of mandatory EMA prompts were limited to two per shift: one at the start and one at the end of the workday. Additional EMA entries were linked to the scanning of the NFC tags, enabling context-specific data collection while reducing the need for separate prompts. These intermediate assessments were optional and could be skipped without consequence if participants felt rushed, overwhelmed, or otherwise unable to respond at the moment.

Furthermore, we actively monitored the acceptability and perceived burden of the EMA procedure through qualitative feedback. Participants were interviewed midway through the assessment period and again at the end, where they were asked about the extent to which the EMA prompts were experienced as disruptive or burdensome. While a detailed analysis of this qualitative feedback is beyond the scope of this paper, these data are being prepared for publication in a separate manuscript focusing specifically on participants’ subjective stress perception, including their experiences with EMA in high-demand clinical settings.

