Regarding the study population, the final sample (n=12) includes no stratified analysis plan based on shift, age, or prior burnout, limiting subgroup insights as a result of the study design. There is also a self-selection bias risk. Participants volunteered, likely introducing selection bias; for example, more tech-savvy nurses participated. However, we do not believe that only more resilient nurses participated in the study. Indeed, it is likely that interest in the study results and the resulting reductions in stress led to increased participation among a group of nurses who demonstrated even lower levels of resilience to stress.

Nurse shortages and the high emotional and physical demands of palliative care contribute to chronic workplace stress, which can undermine both staff well-being and patient care quality. Yet, traditional methods of stress assessment (eg, surveys and end-of-shift reports) often fail to capture the real-time, fluctuating nature of stress in these settings. By using digital monitoring tools such as EMA and physiological sensors, we aim to better understand the moment-to-moment stress patterns nurses experience during their shifts. This approach not only captures stress more accurately but could inform future targeted interventions or adaptive support systems, especially in the strained setting of palliative care where staffing and resilience are critical. The effects of these targeted interventions could then be evaluated by using similar methods to ensure comparability while adding measures for practical relevance such as stress-related attrition (eg, burnout or leaving the profession).

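### Predictability of stress is to be examined by a regression on repeated ratings from 12 nurses, with no nurse-level validation and no benchmark without physiology stated for it or for the AI models

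*Protocol article*

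**What the plan says.** The Data Analyses section of the protocol article states the aim: "To examine the predictability of experiencing stress, the subjective ratings given in the EMA will be used as ground truth". It then gives the model: "A linear regression will be computed with the subjective stress level (EMA) as the dependent variable", "entering the means of the physiological variables (HR, HRV, tonic EDA, phasic EDA, temperature, and acceleration) as independent variables". These are means over data windows around each rating.

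The next sentence allows AI approaches without naming any. The Future Directions section adds a fully connected neural network for regression, with a target between 0 and 100%. The abstract also mentions machine learning once enough data are available.

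On the data, Sample and Recruitment gives 12 consenting nurses out of 18 and says that no power analysis was done. It adds: "The measurement period for each participant was 6 weeks". Each nurse gives many ratings. Strengths and Limitations says: "The number of mandatory EMA prompts were limited to two per shift". Optional ratings follow scans of the tags on the ward.

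No section mentions held-out ratings, held-out nurses, cross-validation, a nurse effect in this regression or a benchmark without physiology. Nor does any section say which measure of fit would settle whether stress is predictable.

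**The concern.** The aim is worded as prediction, but the regression as described estimates association. R-squared computed on the ratings used for fitting cannot fall below zero, so by itself it cannot show that the signals fail to predict.

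Two features of the data make the gap between fit and prediction wider than usual. First, the independent units are 12 nurses, not several hundred ratings. If nurses differ in their usual rating and in their usual sensor values, six predictors can line up with 12 nurse levels by chance. Second, the relation between signal and stress may differ between nurses, even in sign. A common slope fitted to 12 such nurses picks up their chance average, which need not carry over to a thirteenth.

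This matters because the article points beyond the sample: "This approach not only captures stress more accurately but could inform future targeted interventions or adaptive support systems". Support of that kind would have to work for nurses whose ratings did not train the model. The neural network has more freedom to adapt to 12 nurses than a six-term regression, so the same gap could be larger there.

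**Working it through.** **Inputs from the article.** 12 nurses (12/18 = 66.7%, which reproduces the stated 67%), six predictors, one pooled linear regression, repeated ratings over six weeks. The article gives no R-squared, power or error rate for this regression, so there is no further figure to reproduce.

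**Assumed inputs, because the article gives none.** Ratings per nurse: 20 to 200. As an illustration, five shifts a week and two ratings per shift over six weeks give 5 × 2 × 6 = 60. Share of variance lying between nurses (ICC): 0 to 0.5 for ratings and 0 to 0.8 for sensor means. Standard deviation of nurse-specific slopes around zero: 0.15 to 0.25, with predictors and residual standardised.

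**Step 1: fitting and assessing on the same ratings, with no nurse differences.** With p predictors unrelated to the outcome and n independent ratings, expected R-squared is p/(n - 1).
- 30 ratings per nurse, n = 360: 6/359 = 1.7%
- 60 ratings per nurse, n = 720: 6/719 = 0.8%
- 120 ratings per nurse, n = 1440: 6/1439 = 0.4%

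The ordinary F-test stays close to 5%. This part is small.

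**Step 2: nurses differ in level and the regression has no nurse term.** Data were simulated with no relation between predictors and ratings. Leave-one-nurse-out R-squared is 1 - Σ(y - ŷ)²/Σ(y - m)², where ŷ comes from the model fitted to the other 11 nurses and m is the mean rating of those 11. Results for 60 ratings per nurse:

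| ICC ratings / sensors | In-sample R² (mean) | F-test significant | Leave-one-nurse-out R² (mean) | Share of runs above 0 |
|---|---|---|---|---|
| 0 / 0 | 0.009 | 5.6% | -0.009 | 7.5% |
| 0.3 / 0 | 0.009 | 6.3% | -0.008 | 9.2% |
| 0.1 / 0.1 | 0.012 | 20.9% | -0.014 | 9.0% |
| 0.3 / 0.3 | 0.044 | 89.1% | -0.046 | 13.9% |
| 0.5 / 0.5 | 0.108 | 99.3% | -0.109 | 16.5% |
| 0.5 / 0.8 | 0.178 | 99.8% | -0.236 | 18.7% |

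With rating ICC 0.2-0.4, sensor ICC 0.5 and 30 to 120 ratings per nurse, mean in-sample R-squared is about 5-10% and leave-one-nurse-out about -5% to -10%. The inflation needs both ratings and sensor means to differ between nurses: the 0.3 / 0 row shows none beyond Step 1.

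**Step 3: level differences removed, slopes differ.** Ratings and predictors were centred within nurse, and nurse slopes were drawn around zero with SD 0.15-0.25. Mean in-sample R-squared is about 2-5% (1.4-4.0% in one set of runs). Leave-one-nurse-out R-squared is about -2% to -5%. The ordinary F-test was significant in 27-92% of runs in one set and 38-96% in another, more often with more ratings. Removing nurse levels alone therefore does not close the gap.

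**Step 4: is a cross-validated R-squared above zero enough?** Across the Step 2 settings and rating counts it exceeded zero in about 6% to 19% of runs with no predictability. A bare above-zero rule would be too lenient.

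**The case against.** The strongest reply is that the article does not say what a critic might infer from it. A reader might conclude that predictability will be judged from fit on the same ratings and that a small positive R-squared will be reported as success. The text says neither. It gives no assessment rule, it is a condensed article, and a validation scheme could stand in a fuller plan. This stands, and it limits the point to what is written: a predictive aim, a named model and no nurse-level check.

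It can also be said that the study seeks correlations. Feasibility is the primary outcome, correlations are secondary, and future support systems are mentioned only as a possibility. A regression suits that aim, and if the result is called association the point largely falls away. But the Data Analyses section itself chose the language of prediction and ground truth.

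Third, much of the size comes from nurse differences that the article does not quantify. The larger figures reflect a missing nurse term, which is a repeated-measures problem. Same-data fitting alone adds little. That is correct. Step 3 shows, however, that a gap remains once nurse levels are removed. One may answer that with non-zero slopes stress is related to physiology within each nurse. That is fair: Step 3 shows failure to transfer to another nurse, not absence of any relation.

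**Conclusion.** The point holds in a limited form. The article names predictability as the aim and specifies the model, outcome and predictors. For neither that regression nor the AI and neural-network models does it state a nurse-level validation or a benchmark without physiology. In-sample fit would support a statement about association in these 12 nurses only.

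The possible size is an in-sample R-squared of about 5-10% without a nurse term, or about 2-5% after centring within nurse with varying slopes, against about -2% to -10% in a nurse left out. These ranges rest on assumed ICCs, slope SDs and rating counts. If nurses hardly differ, the inflation is only about 0.4-1.7%.

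The documents do not support the stronger reading that a positive fit will be taken as predictability, or that same-data fitting is materially misleading whatever the nurses are like. This is an improvement that should be made, with medium confidence, not a demonstrated error.

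**What to change.** State that predictability, for the regression and for any AI or neural-network model, will be assessed by leave-one-nurse-out cross-validation: fit on 11 nurses, predict the twelfth, and repeat for all 12. Do all scaling, variable selection and tuning inside the training nurses. Refit any model already trained on all nurses within each fold. A random split of ratings is not a substitute, because the same nurses would be on both sides.

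Report cross-validated R-squared and mean absolute error in slider points against a benchmark without physiology. For prediction in a new nurse the benchmark is the mean of the other nurses. For separating higher from lower ratings within a nurse it is that nurse's own mean. Attach a nurse-level interval or a nurse-level permutation test, not a bare above-zero rule. Report in-sample fit as association only. If this validation is not wanted, replace predictability by association in the text.

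The cost is a few sentences and a small amount of new code. The article uses Python for data extraction and SPSS for the inferential analyses, so the loop has to be written. It must be run at the research institute that holds the individual-level data, since the hospital receives only averaged data. No new data are needed. The figure will be less favourable and, with 12 nurses, imprecise.
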